### Local reactions

Minor bleeding at the needle point.

Subcutaneous bruise.

Subcutaneous haematomas.

Pain in the operated area after operation.

Local allergy in the punctured region after treatment.

Local infection.

Local nodules.

### Systemic reactions

Dizziness or fainting during or after treatment.

Systemic allergy.

Systemic infection.

For patients with common adverse reactions, appropriate medical care will be given to ease local bleeding, bruising and so on.

Severe AEs are defined as symptoms or diseases that result in hospitalization or prolonged hospitalization, disability, a life-threatening situation or even death. In this trial, systemic infection and allergy are two major severe AEs. Severe AEs will be reported to the Ethics Committee within 24 hours. The Ethics Committee will provide medical suggestions for the research team and decide on whether the patient should continue with the ongoing treatment. Proper compensation will be given to cover their medical costs.

### Modification of the protocol

Any modifications to the protocol, including changes to the study objectives, study design, patient population, sample sizes, study procedures or significant administrative aspects, will require a formal application to the Zhejiang Provincial Administration of Traditional Chinese Medicine as well as the Chinese clinical trial registry.

### Dissemination

Initial data will be accessible through the Research Manager (ResMan). The results of this study will be published in open-access and peer-reviewed journals or presented at relevant conferences.

## Discussion

Acupuncture is widely used to treat PFP after the acute stage in China [27–29]. It is commonly used to treat FEMA after PFP. However, many patients find it difficult to adhere to it since it requires about three treatments per week. TEA is a new type of acupuncture with a low treatment frequency (once a week). The suture threads, such as polyglycolic acid which has good biodegradability and biocompatibility [30], are widely used in TEA in China. The TEA-embedded thread can increase the tensile strength and stimulate myoblast formation in connective tissues [21, 31], which is considered to be the basis for the clinical application of this treatment.

Herein, STEA is used to determine the effect of specific intervention factors. STEA will be applied to minimize the needle insertion effect since the penetration of traditional acupuncture can be used to treat muscular atrophy. Participants, assessors, and statisticians will be blinded to the groups to minimize comparison bias.

B-ultrasonography is widely used to measure muscle or other soft tissues and disease diagnosis [32]. It is a sensitive detection method for facial muscle thickness and safe, non-invasive, simple to operate, and cost-effective [33–35]. Studies have shown that normal humans have no significant differences in bilateral expression muscle thickness [36, 37]. Therefore, the thickness of healthy facial expression muscles can be used to detect the atrophic facial expression muscle side. Herein, the test was performed at weeks 0 and 10. The final test will be set at two weeks after treatment because improvements of the muscle structure and strength need a long time for recovery.

Moreover, facial expression muscle function recovery is essential for the evaluation of FEMA treatment using TEA. The physical functions will be assessed via H-B Grade and lip mobility score as the secondary outcome measures.

However, this study has some limitations since it is not designed for a stratified study. There are differences in FEMA recovery after PFP with different disease courses. Stratified observation can screen out the best efficacy group with certain disease courses, giving accurate guidance of TEA timing for clinical treatment of FEMA after PFP.

In summary, this study will evaluate the efficacy and safety of TEA for FEMA after PFP. These findings will enhance understanding of TEA as a therapeutic option for FEMA patients after PFP.

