#### Inclusion criteria

Patients will be eligible for the study if they:
Male or female patients aged 18–65 years.Patients diagnosed with peripheral facial paralysis ≥3 months before screening.Patients with H-B Grade ≥III.Patients with atrophic facial expression muscles as revealed by B-mode ultrasonography. The muscle thickness of the affected side/healthy side ≤ 90%.

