### Allocation

After completing a baseline evaluation, eligible participants will be randomly assigned to either the intervention or the sham-controlled group in a 1:1 ratio by an independent investigator. Subjects in the intervention group will receive TEA treatment, whereas the subjects in the sham-controlled group will receive the sham treatment. Random numbers will be generated by a statistician from the Clinical Evaluation and Analysis Centre of The First Affiliated Hospital of Zhejiang Chinese Medical University using SPSS for Windows (Version 22.0; SPSS Inc., Armonk, NY, USA). Sealed opaque assignment envelopes were used for allocation concealment. Those envelopes will be stored in a locker and the key kept by the clinical research coordinator (CRC). CRC will offer the envelopes that correspond to the group allocation to the acupuncturist after completion of recruitment.

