### Data processing and statistical analysis

Following the intention-to-treat principle, data processing and analysis will be performed at the Clinical Evaluation and Analysis Centre of The First Affiliated Hospital of Zhejiang Chinese Medical University. These analyses will be performed on the base of a full analysis set (FAS) and a per-protocol set (PPS). All efficacy analyses will be performed using a FAS, which will consist of all patients who passes the randomized stage and who receives at least one intervention. Last observation carried forward (LOCF) analysis will be used for missing data imputation. The PPS will be considered as a supportive analysis. The results of FAS and PPS analyses will be compared to ensure that the results are consistent. A generalized linear mixed-effect model will be used for sensitivity analysis via the PPS. A subgroup analysis will be conducted following the Kellgren–Lawrence grade.

Quantitative results will be described by the mean, standard deviation, median (quartile 3–1, Q3–Q1), minimum, and maximum, while qualitative results will be expressed as total number and percentages. Grade results with rank meaning will be described via both quantitative and qualitative methods.

The chi-square test will be used to compare the primary outcomes between the two groups. The Wilcoxon rank-sum test will be used to compare ranked data and the independent samples t-test for secondary outcome measures to analyze continuous variables. The incidence of adverse events will be determined and compared between the two groups for safety outcomes. A p-value of <0.05 will be considered statistically significant. SPSS Statistics V.22.0 will be used for all analyses. An interim analysis will be conducted when 50% of the randomized patients completed the primary outcome measurement.

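### The protocol says recovery differs with disease course, but its main between-group tests use neither time since diagnosis or onset nor the baseline value, which costs precision and leaves chance imbalance uncorrected

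*Protocol article*

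**What the plan says.** All places are in the protocol article.

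- **Discussion.** The authors write "There are differences in FEMA recovery after PFP with different disease courses". The sentence after it speaks of guiding the timing of TEA, so disease course here means duration. They also concede that "this study has some limitations since it is not designed for a stratified study".
- **Inclusion criteria.** The entry rule is "Patients diagnosed with peripheral facial paralysis ≥3 months before screening". Neither the inclusion nor the exclusion criteria set a maximum.
- **Allocation.** Participants are "randomly assigned to either the intervention or the sham-controlled group in a 1:1 ratio by an independent investigator". No stratum, block or minimisation factor is named.
- **Data processing and statistical analysis.** For the primary outcome, "The chi-square test will be used to compare the primary outcomes between the two groups". For the rest, "The Wilcoxon rank-sum test will be used to compare ranked data and the independent samples t-test for secondary outcome measures". None of these tests takes a covariate. The one model appears as "A generalized linear mixed-effect model will be used for sensitivity analysis via the PPS", with no covariates listed. The one subgroup analysis is by Kellgren–Lawrence grade, not by duration.

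**The concern.** The protocol itself names a factor that it expects to drive recovery, admits patients across an open-ended range of that factor, and then leaves it out of both the allocation and the main comparison. The baseline thickness ratio, which is measured anyway, is left out as well.

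Two things are at stake. First, variation that duration and the baseline value could explain stays in the error term, so confidence intervals are wider than they need be. Second, with 28 patients per arm, the arms can differ by chance in how long patients have been affected. If that happens, the unadjusted difference absorbs part of it, in favour of TEA or against it, and no main analysis corrects for it.

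The point concerns adjustment of the main effect. It is not a request for a subgroup analysis by duration.

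**Working it through.** **Inputs from the Sample size section:** SD 23.30, difference 21.54, two-sided alpha 0.05, power 0.90, dropout 10%, ratio 1:1. The section does not say which outcome these figures describe. I take them to be on the scale of the primary outcome.

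**Reproducing the plan's own figure.** n = 2 × 23.30² × (1.960 + 1.282)² / 21.54² = 24.59, rounded up to 25 per arm. Dropout: 25 / 0.90 = 27.8, so 28 per arm. The stated number reproduces. The standardised difference is 21.54 / 23.30 = 0.92.

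**Gain in precision from adjustment.** Let R² be the share of outcome variance that the added covariates explain within arms. It is not in the documents; I assume 0.1 to 0.3. The residual SD is 23.30 × √(1 − R²), and the interval width scales with the same factor. Power is for a two-sample t-test with 25 evaluable per arm.

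| R² (assumed) | √(1 − R²) | Interval narrower by | Power at 21.54 |
|---|---|---|---|
| 0 (plan) | 1.000 | – | 89.3% |
| 0.1 | 0.949 | 5% | 92.2% |
| 0.3 | 0.837 | 16% | 96.9% |

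**Does the unadjusted test keep its level?** In 40,000 simulated trials with 25 per arm and covariate–outcome correlation ρ of 0.3, 0.5 and 0.7, the t-test rejected a true null in 4.9% to 5.0% of trials and had about 89% power at the planned difference. Covariance analysis also held about 5% and reached 91%, 96% and 99% power. Over all randomisations, the unadjusted test is valid.

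**How large can imbalance be, and what does it do?** The standardised between-arm difference in a continuous covariate has SD √(2/n). At 28 per arm this is 0.267, so P(beyond 0.25 SD) = 35% and P(beyond 0.5 SD) = 6%. At 25 per arm the SD is 0.283 and P(beyond 0.5 SD) = 8%.

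Given an imbalance of 0.5 SD, the shift in the estimate is ρ × 0.5 × 23.30. With 25 per arm the standard error is 23.30 × √(2/25) = 6.59. Conditional rejection rates use a normal approximation with spread 6.59 × √(1 − ρ²):

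| ρ (assumed) | Shift (points) | Type I error given the imbalance | Power if it runs against TEA |
|---|---|---|---|
| 0.2 | 2.3 | 6.0% | 83.5% |
| 0.3 | 3.5 | 7.2% | 79.3% |
| 0.5 | 5.8 | 10.8% | 68.8% |
| 0.7 | 8.2 | 15.6% | 54.0% |

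The comparison value without conditioning, by the same approximation, is 90.5% power. At a smaller imbalance of 0.25 SD, the conditional type I error is 3.0% to 4.9%, that is, not raised at all.

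**The case against.** **Randomisation already allows for this.** Chance imbalance is part of the sampling error that the test is built on. That stands: the simulation shows about 5% type I error and about 89% power without adjustment. A reader might infer that the omission inflates the false-positive rate or invalidates the comparison; it does neither. What remains is precision, and the estimate in the one allocation that is realised.

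**The authors disclose the lack of stratification.** They do, but they regret only a lost chance to find the duration group that responds best. They do not address imbalance between arms and offer no remedy in the analysis.

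**The Discussion may mean differing response to treatment.** That reading is possible, since the next sentence is about efficacy and timing. A reader might also infer that early patients recover spontaneously and that this recovery passes for a TEA effect. The protocol does not speak of natural recovery, and its background says that the atrophy can persist if not properly treated. The point needs only the protocol's statement that recovery differs with course; how strongly remains unknown.

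**An analysis plan may list covariates.** For the mixed model it may, and it would be wrong to say that every planned analysis is an unadjusted two-group test. For the main comparisons, however, the article names tests that take no covariates. Adding adjustment there changes the stated method; it does not fill in a detail.

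**The allocation may be blocked.** The text does not say that randomisation is simple. Blocking without strata would not balance duration in any case.

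**The size rests on assumptions.** It does. Splitting patients into early and late shows how fragile such figures are. With half assumed early, a gap of at least 20 percentage points has probability 18.1% at 28 per arm and 25.8% at 25 per arm. At a cut of 21 points the figures are 18.1% and 8.9%. That contrast between arm sizes is an artefact of whole-patient counts and should not be read as a loss from dropout.

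**Conclusion.** The point holds as a missed gain in precision and a missing safeguard against chance imbalance. It does not show an invalid test, an inflated overall type I error or an underpowered trial: on its own inputs the plan has about 89% power with 25 evaluable per arm before any adjustment.

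The gain is a 5% to 16% narrower interval and power of 92% to 97%, if the covariates explain 10% to 30% of the variance. An imbalance of 0.5 SD, which has a probability of 6% to 8%, would shift the estimate by 2.3 to 8.2 points for ρ from 0.2 to 0.7, against the planned 21.54. At ρ of 0.2 to 0.3 the effect is small. Neither R² nor ρ is in the documents, nor do they show how much duration adds beyond the baseline ratio. The change is worth making because it costs little.

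**What to change.** Before the interim analysis, amend the analysis section as follows.

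1. **Primary outcome.** Replace the chi-square test with a linear model of the week-10 thickness ratio on treatment, baseline ratio and log months since diagnosis or onset. This openly changes the stated test: the thickness ratio is continuous, and a chi-square test can neither use it as such nor take these covariates.
2. **Lip indices.** Use the same form of model, with the baseline value of each index, in place of the t-test.
3. **H-B Grade.** Use an ordinal model with treatment, baseline grade and log months since diagnosis or onset, in place of the Wilcoxon test.
4. **Baseline data.** Record the date of diagnosis or onset as a baseline item, state which of the two it is, and define it for patients with more than one episode. The entry rule can be met by a yes/no check, and the article does not say that the date itself is kept.

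Allocation and sample size stay unchanged. Patients already randomised are unaffected, provided that their date can be taken from the screening record. The cost is one recorded date and a model-based analysis in place of simple tests. Fixing the covariates before the look at 50% avoids the appearance of a choice driven by the data.

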### Trial status

This study protocol version number is 1.0, dated 10 July 2019. The participants have been recruited for the present study since October 2020. Ten patients are under treatment. And the recruitment will be completed in March 2022.

## Data Availability

The datasets used and analyzed during the current study are available from the corresponding author on reasonable request.

## Abbreviations

PFP: Peripheral facial paralysis
FEMA: facial expression muscles atrophy
TEA: thread-embedding acupuncture
STEA: sham thread-embedding acupuncture
CRF: Case report form
H-B Grade: House-Brackmann Grade
LL-index: lip-length index; S-index: snout index
CRC: clinical research coordinator
FAS: full analysis set
PPS: per-protocol set
LOCF: last observation carried forward
DMC: data monitoring committee
DSMB: Data and Safety Monitoring Board
AEs: adverse events
